#### Disease characteristics

Diagnosis, disease duration (in years since diagnosis) and number of co-morbidities are asked. The diagnosis is checked by a rheumatologist.

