### Sample size

The sample size calculation is based on depressive symptoms as a primary objective. In order to demonstrate a medium-sized effect (Cohen’s *d* = 0.40), 100 participants in each condition are required, based on a statistical power (1-beta) of 0.80, a two-sided test and an alpha of 0.05 (power calculation with G-power).

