#### Effectiveness analysis on primary and secondary outcome measures

To examine differences between the two conditions on all outcome measures, analysis of variance for repeated measures (group x time) will be used. If demographic or outcome measures differ significantly between the groups at baseline, these measures will be incorporated into the analysis as covariate(s). Planned polynomial contrasts are used to analyze differences in effect of the program post-intervention and after the follow-up in the experimental group. Effect sizes of the experimental group in primary and secondary outcomes at post-intervention and follow-up will be calculated with Cohen’s D using the means and pooled standard deviations of the measurements of the conditions. Effect sizes are considered according to Cohen [79] as follows: small d=0.2, medium d=0.5, and large d=0.8. To see if subgroups (e.g., high/low age, gender, disease severity) respond better to the program, subgroup analyzes will be calculated using independent t-tests or Mann–Whitney tests.

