### Strengths and limitations of the randomized controlled trial

Our study will hopefully answer questions regarding the effectiveness of the goal management intervention for patients with a rheumatic disease. We try to understand the pathways that are responsible for successful adaptation in persons dealing with a rheumatic disease and investigate who benefits most. In addition, we have included an economic evaluation. However, these additional analyzes cannot be conducted in absence of an effect of the goal management intervention compared to the waiting list group.

As the “Right On Target” program is a newly developed intervention, we execute a stakeholders’ analysis. Experiences of participants, trainers and the management of the participating clinics provides insight into the feasibility regarding the intervention. The information from the stakeholders’ analysis supports future implementation of the intervention.

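### The two-sample tests planned for subgroups cannot show whether the program's effect differs between subgroups; an arm-by-subgroup interaction is needed

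*Protocol article*

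**What the plan says.** The question and the test stand in one sentence of the protocol article, section *Effectiveness analysis on primary and secondary outcome measures*: "To see if subgroups (e.g., high/low age, gender, disease severity) respond better to the program, subgroup analyzes will be calculated using independent t-tests". The Mann–Whitney test is named as the alternative.

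The sentence does not say which two samples are compared. They could be two subgroups of program participants, or the two arms within each subgroup. For the main effectiveness analysis the same section says that "analysis of variance for repeated measures (group x time) will be used". Group by time is the only interaction named there, and no term combining arm and subgroup appears anywhere in the article.

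The Discussion, under *Strengths and limitations of the randomized controlled trial*, says the authors also want to "investigate who benefits most". It adds that the additional analyses depend on the intervention showing an effect against the waiting list.

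**The concern.** Whether one subgroup responds better is a question about effect modification. The quantity of interest is (program minus control in subgroup a) minus (program minus control in subgroup b), which needs four cells. An independent t-test or a Mann–Whitney test compares two samples, so under either reading it answers another question.

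- **Subgroups compared inside the program arm.** There is no control comparison. Older and younger patients, for example, may follow different courses without any program. Entry requires a HADS depression score of four or higher, so some regression to the mean is also plausible, and it need not be equal across subgroups. Change scores reduce differences in starting level but leave both problems in place.
- **Arms compared separately in each subgroup.** Each test is valid for its own subgroup, but the contrast between two p-values is not a test of difference. The larger subgroup is favoured by its size alone.

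At stake is a published statement that the program works better for some patients than for others when the data do not show it. Because the test is named, an analysis plan that followed this sentence would carry the problem forward.

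**Working it through.** **Inputs from the article.** *Sample size*: "In order to demonstrate a medium-sized effect (Cohen’s *d* = 0.40), 100 participants in each condition are required". The calculation behind this number is described as "based on a statistical power (1-beta) of 0.80, a two-sided test and an alpha of 0.05". *Randomization*: 1:1 allocation.

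**Assumptions (not in the article).** Subgroup splits of 50/50, 30/70 and 25/75, the same in both arms. A difference g in natural course between subgroups of 0 to 0.5 SD. The same true effect, d = 0.40, in every subgroup. One analysed score per patient with SD 1, and all 100 per arm analysed.

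**Step 1: reproduce the plan's figure.** Normal approximation: n = 2 × ((1.960 + 0.842)/0.40)² = 98.1, so 99 per arm. The exact two-sample t-test (non-central t) needs 100 per arm, with power 0.804. The stated 100 is reproduced.

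**Step 2: subgroups compared inside the program arm (100 patients).** SE = √(1/n_a + 1/n_b), non-centrality = g/SE, 98 degrees of freedom, two-sided 0.05. At 50/50, SE = √(1/50 + 1/50) = 0.200. At 30/70, SE = √(1/30 + 1/70) = 0.218. The program effect is the same in both subgroups, so every significant result is a false finding of better response.

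| g (SD) | 50/50 | 30/70 |
|---|---|---|
| 0 | 0.050 | 0.050 |
| 0.2 | 0.168 | 0.148 |
| 0.3 | 0.318 | 0.275 |
| 0.4 | 0.508 | 0.442 |
| 0.5 | 0.697 | 0.621 |

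**Step 3: arms compared separately in each subgroup.** With m patients per arm in a subgroup, SE = √(2/m) and non-centrality = 0.40/SE. For m = 50 this is 0.40/0.200 = 2.0. If the two powers are p₁ and p₂, exactly one test is significant with probability p₁(1 − p₂) + p₂(1 − p₁).

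| Split | Power, smaller | Power, larger | Exactly one significant |
|---|---|---|---|
| 50/50 | 0.508 | 0.508 | 2 × 0.508 × 0.492 = 0.50 |
| 30/70 | 0.332 | 0.652 | 0.332 × 0.348 + 0.652 × 0.668 = 0.55 |
| 25/75 | 0.283 | 0.682 | 0.283 × 0.318 + 0.682 × 0.717 = 0.58 |

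At 30/70 only the larger subgroup is significant in 0.652 × 0.668 = 0.44 of trials, and only the smaller in 0.332 × 0.348 = 0.12.

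**Step 4: arm-by-subgroup interaction.** SE = √(2/n_a + 2/n_b), with n_a and n_b the subgroup sizes per arm. This is 0.283 at 50/50 and 0.309 at 30/70.

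- False-positive rate, from 20,000 simulated trials with 50 per cell and a common effect of 0.40: 0.050 with g = 0 and 0.050 with g = 0.4. In the same simulations the within-arm test of Step 2 rejected in 0.049 and 0.505.
- Power for an interaction of 0.40 SD (normal approximation): 0.40/0.283 = 1.41 gives 0.29 at 50/50; 0.40/0.309 = 1.30 gives 0.25 at 30/70.
- Interaction detectable with 80% power: 2.80 × 0.283 = 0.79 SD at 50/50 and 2.80 × 0.309 = 0.86 SD at 30/70.
- Sample needed for an interaction of 0.40 SD at 50/50: 8 × (2.80/0.40)², about 393 per arm with unrounded constants.

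**The case against.** The strongest defence is that this is a secondary, exploratory step in a condensed article, and that several damaging readings go further than the text. Much of that stands.

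- **Standing of the question.** A reader might infer that finding out who benefits most is a formal aim that will steer implementation. *Aims of the current study* lists no subgroup aim. The phrase occurs only in the Discussion, and the article links implementation to the stakeholders' analysis.
- **Disease severity.** A reader might infer that it cannot be measured, since the article says "Diagnosis, disease duration (in years since diagnosis) and number of co-morbidities are asked". But it is given only as an example, its definition can be left to the analysis plan, and pain, fatigue and physical functioning are all measured at T0.
- **High/low age.** Splitting age is inefficient but not an error in an exploratory description, and no cut-point is stated. Continuous age is a preference.
- **The error rates.** No single false-positive rate follows from the article. The Step 2 figures depend on an assumed prognostic difference and fall to 5% when there is none. The 50–58% in Step 3 is not the error rate of any test. It becomes an error only if one significant and one non-significant result are read as a difference.
- **The condition of an overall effect.** This guards against a subgroup search after a null main result. It does not cure the choice of test, because every figure above already assumes a real common effect of d = 0.40.

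The core is untouched. The article names the test, so this is not detail left to another document, and the test cannot answer the question set for it.

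**Conclusion.** The point holds as a defect in a secondary analysis. Under either reading of the sentence, the planned tests do not assess whether the program's effect differs between subgroups. The size depends on quantities the article does not give. With 100 per arm and a common effect of 0.40 SD, a within-arm comparison goes wrong in 17% to 70% of trials at a 50/50 split (15% to 62% at 30/70) for differences in natural course of 0.2 to 0.5 SD. Separate comparisons disagree in about half of trials or slightly more. Misreading is therefore a risk, not a certainty.

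A reader might infer that the trial's main conclusion is compromised. It is not: the test of depressive symptoms between arms does not depend on this sentence. The correct test would also seldom settle the question at this sample size, so subgroup findings should be presented as exploratory whatever they show.

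**What to change.** Replace the sentence on t-tests and Mann–Whitney tests. For each subgroup variable, extend the planned repeated-measures model with that variable and its interactions, using both arms. The term of interest is arm by subgroup by time, because in that model the program effect is itself the group-by-time term. Report the interaction estimate with its 95% CI and label it exploratory. Keeping age continuous is preferable. Effects within each subgroup can still be shown descriptively, without basing a claim of difference on their separate p-values.

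The cost is a change of wording. No new data are needed, and the main effectiveness model stays as specified. The drawback is low power, about 25–29% for an interaction as large as the planned main effect, so few subgroup differences could be claimed and a non-significant interaction would not show that the effect is uniform.

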#### Analysis of mediation

Multiple mediation analysis will be performed to analyze whether the tendencies to use goal management strategies and coping versatility mediate the effects in the intervention. Primary and secondary outcomes used are the measures of depression, anxiety, purpose in life, positive affect and participation. Baseline and post-intervention measurements of both intervention and waiting list group will be used. A change score for tendencies to use goal management strategies and coping versatility will be computed with scores from baseline and post-intervention measurement. Multiple mediation analysis with bootstrapping procedures (n = 5000 bootstrap re-samples) will be used to assess the indirect effect of the mediation pattern, as recommended by Preacher and Hayes [80]. An indirect effect will be considered significant in the case when zero is not contained in the 95% bias-corrected confidence interval. Self-efficacy pain and self-efficacy for other symptoms will be incorporated in the multiple mediation analyzes as putative mediators. To analyze whether the GSMV mediate the effects of the intervention on the primary and secondary outcome measures, dummy variables will be used to indicate whether or not a strategy is named.

#### Economic evaluation

Results will be expressed as quality-adjusted life years (QALYs). The time-integrated summary score, which is the area under the curve (AUC) of the utilities, will be calculated to define the quality of life per time period (0–2 months and 0–8 months). Between-group differences in QALYs will be analyzed per period using t-test for unpaired observations. The costs will be presented as an arithmetic mean (+− SD) per patient per group. The between-group differences in resource use will be analyzed per period using the Mann–Whitney U test. For every patient and study period, the mean incremental costs will be calculated, and, using double-sided bootstrapping, 95% confidence intervals (95%CI) will be estimated. The incremental cost utility ratio (ICER) will be calculated by dividing the extra costs for the goal management intervention by the extra QALYs derived from the goal management intervention. The ICER will be expressed as costs per QALY gained. The 95% confidence intervals of the ratios will be estimated with bootstrapping. Cost evaluations will be conducted from the societal perspective and with a time-horizon of less than one year. Due to this short time-horizon, costs and effects will not be discounted.

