### Randomization

The participants are assigned in a 1:1 ratio to either the experimental group or the control group. Patient allocation is be done by means of blocked stratified randomisation per site in random block sizes of 2 and 4 to make sure that both conditions are equally distributed in each participating hospital. The study is open label, as it is impossible, due to the nature of the program, to blind the staff and participants involved to the condition which the patient is allocated.

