### Measures for the economic evaluation

#### Utilities

The EuroQol-5D (EQ-5D) [74,75] is used to assess utilities. The EQ-5D descriptive system consists of five dimensions: mobility, self-care, usual activities, pain/discomfort and anxiety/depression [75]. Furthermore, the ‘thermometer’ is asked; patients rate their health status on a scale from 0 (worst possible health) to 100 (best possible health).

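### The economic evaluation compares QALYs without adjusting for baseline utility, puts a confidence interval on the cost/QALY ratio, and is made conditional on an undefined effect that the aims do not require

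*Protocol article*

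**What the plan says.** **Utilities.** "The EuroQol-5D (EQ-5D) [74,75] is used to assess utilities". Table 3 lists the instrument at T0, T1 and T4, so a baseline utility exists for each participant.

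**QALYs.** The Economic evaluation section takes the area under the utility curve for 0–2 and 0–8 months and then says: "Between-group differences in QALYs will be analyzed per period using t-test for unpaired observations". It names no covariate. The article's only baseline-covariate rule is in the section on effectiveness analysis of primary and secondary outcomes. It belongs to the repeated-measures ANOVA and is triggered by a significant baseline difference.

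**Ratio.** The ICER is extra costs divided by extra QALYs, and "The 95% confidence intervals of the ratios will be estimated with bootstrapping".

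**Condition.** The section on strengths and limitations of the trial mentions the economic evaluation and continues: "these additional analyzes cannot be conducted in absence of an effect of the goal management intervention compared to the waiting list group". The aims section and the abstract present the cost-effectiveness analysis as planned, with no such condition, and the Economic evaluation section contains none.

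**The concern.** Three stated choices weaken the cost-utility answer.

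1. Baseline utility is part of the area under the curve and is correlated with the later utilities. Leaving it in the outcome without adjusting for it adds removable noise to the QALY difference.
2. A ratio does not order results sensibly when its denominator can change sign. A negative ratio may mean cheaper and better, or dearer and worse. A positive one may mean dearer and better, or cheaper and worse. Ranking resampled ratios mixes these cases. This is a realistic prospect here: the Background describes self-management effects in inflammatory arthritis as negligible to small, and the horizon is eight months.
3. The article plans the evaluation unconditionally in one place and rules it out in another, depending on an effect that it does not define. Whether the result is produced could then be decided after the clinical data are seen.

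At stake is a stated secondary aim. The primary analysis is not affected.

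**Working it through.** **The plan's own figure.** The Sample size section asks for d = 0.40, "based on a statistical power (1-beta) of 0.80, a two-sided test and an alpha of 0.05", and concludes that "100 participants in each condition are required". The normal approximation gives 2 × (1.960 + 0.842)² / 0.40² = 98.1, so 99 per arm. The two-sample t-test gives 99.08, so 100, with power 0.804. The figure reproduces and is used below as 100 per arm.

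**Inputs from the article.** Allocation is 1:1. The last follow-up is eight months after entry (Control condition) and six months after the programme ends (Measurements), so T0, T1 and T4 fall at about 0, 2 and 8 months. This matches the two QALY periods.

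**Assumptions, not in the documents.** Utility SD 0.20 (range 0.15–0.25), equal correlation ρ between visits of 0.5–0.7, and complete data.

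**Step 1: weights (trapezoid rule, in years).**
QALY(0–8) = [2(u0+u1)/2 + 6(u1+u4)/2]/12 = (u0 + 4u1 + 3u4)/12.
Baseline utility has 1/8 = 12.5% of the total weight over 0–8 months. Over 0–2 months it has 50%.

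**Step 2: standard error without adjustment.**
Var(QALY) = SD² × (26 + 38ρ)/144, and the SE of the difference is √(2 × Var/100).
- ρ = 0.5: 0.20 × √(45/144) × √0.02 = 0.0158
- ρ = 0.7: 0.20 × √(52.6/144) × √0.02 = 0.0171

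**Step 3: standard error adjusted for T0 utility.**
R² = (1 + 7ρ)²/(26 + 38ρ).
- ρ = 0.5: 20.25/45 = 0.45; SE = 0.0158 × √0.55 = 0.0117 (26% lower)
- ρ = 0.7: 34.81/52.6 = 0.66; SE = 0.0171 × √0.338 = 0.0099 (42% lower)

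The percentage reduction does not depend on the SD. At ρ = 0.6 the SE falls from 0.0123 to 0.0082 for SD 0.15, and from 0.0206 to 0.0137 for SD 0.25. For 0–2 months the adjusted variance is 0.25 (ρ = 0.5) or 0.15 (ρ = 0.7) of the unadjusted variance.

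**Step 4: how often the denominator is negative.**
The share is Φ(−ΔQALY/SE). A utility gain g held at T1 and T4 gives ΔQALY = 7g/12.

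| True gain g | ΔQALY | Unadjusted, ρ 0.5 to 0.7 | Adjusted, ρ 0.5 to 0.7 |
|---|---|---|---|
| 0.04 | 0.0233 | Φ(−1.48) to Φ(−1.36) = 7% to 9% | Φ(−1.99) to Φ(−2.35) = 2% to 1% |
| 0.02 | 0.0117 | Φ(−0.74) to Φ(−0.68) = 23% to 25% | Φ(−0.99) to Φ(−1.17) = 16% to 12% |
| 0 | 0 | 50% | 50% |

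For g = 0.04 and ρ = 0.6, the unadjusted share is about 3% at SD 0.15 and 13% at SD 0.25.

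**Step 5: illustration of the ratio.** Take g = 0.02, ρ = 0.6, SD 0.20, an assumed extra cost of 300 euros and an assumed cost SD of 3,000, with costs and QALYs independent. Simulated cost/QALY ratios then have 2.5 and 97.5 percentiles of about −303,000 and +329,000, and 36% of them are negative. Half of those come from the cheaper-and-better quadrant and half from the dearer-and-worse quadrant (18% each). Net monetary benefit at an assumed 20,000 per QALY runs from −1,120 to +987. That interval is wide, but it is finite and ordered.

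**Step 6: the condition.** No arithmetic is needed. The aims and the Economic evaluation section say that the analysis will be done; the Discussion says that it cannot be done without an effect. Mean costs and mean QALYs per arm, and their differences, can be computed from the collected data whatever the clinical result.

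**The case against.** **The t-test is valid.** A reader might infer that chance baseline imbalance biases the QALY difference. It does not. Under 1:1 randomisation the unadjusted comparison is unbiased, and its standard error already includes chance imbalance. This objection stands in full: the gain from adjustment is in precision, on an analysis that is not primary.

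**The ratio interval is not always meaningless.** If the QALY difference is clearly away from zero, the interval is usable. The article does not name a bootstrap type, so no particular one can be criticised. It also plans a test of the QALY difference and an interval for incremental costs, so numerator and denominator can be seen separately. All this stands. But the interval is fixed in advance, when nobody can know that the difference will be far from zero, and no bootstrap variant gives the ratio a sensible ordering across quadrants. That a condensed article omits a cost-effectiveness plane or acceptability curve is not a fault in itself.

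**The condition is a Discussion remark.** A reader might infer that the evaluation will be dropped unless the HADS depression result is significant, and so appear only when the programme looks good. The document does not say this. The word effect is not tied to any outcome or to significance, so no probability of dropping the evaluation can be attributed to the plan. What remains is the contradiction and the incorrect claim that the analysis is impossible.

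**Mediation and subgroups.** The same remark also covers these analyses. Whether to run a mediation analysis after a null total effect is a separate and debatable question, and nothing here turns on it.

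**Conclusion.** The point holds as a matter of precision, reporting and internal consistency, not of bias. The unadjusted t-test forgoes a reduction of 26–42% in the standard error of the 0–8 month QALY difference, for correlations of 0.5–0.7. The ratio interval is at risk of being uninterpretable for any modest gain, and adjustment reduces that risk without removing it. These sizes rest on assumed utility SDs and correlations and on complete data at 100 per arm; the cost figures in the illustration are assumed too.

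The conflict between the Discussion and the aims needs no assumption and is the firmest part. All three elements are worth correcting before analysis.

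**What to change.** 1. Replace the unpaired t-test by a regression of QALYs on arm, T0 utility and hospital (the randomisation stratum), for each period.
2. Resample cost and QALY pairs together by patient. Report incremental costs, incremental QALYs and incremental net monetary benefit over a stated range of thresholds, or an acceptability curve. Drop the confidence interval on the ratio.
3. Delete the condition in the section on strengths and limitations of the trial as far as it concerns the economic evaluation, and state that the evaluation will be reported whatever the clinical result.

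The cost is a change of wording and a little more analysis work. No new data are needed, since utilities at T0 and costs are already collected.

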Utilities	T0, T1, T4	EQ-5D	Brooks, 1996 [74]; Lamers, McDonnell, Stalmeier, Krabbe, & Busschbach, 2006 [75]	I have no problems in walking about.	1-3	-	15	No problem (1) - extreme problems (3)
Direct medical costs	T0, T1, T2, T3, T4	-	-	See article’s text	N.A.	N.A.	3	Open ended
Indirect non-medical costs	T0, T1, T2, T3, T4	-	-	See article’s text	N.A.	N.A.	7	Open ended
Price estimate	T1	-	-	See article’s text	N.A.	N.A.	1	In euros for de complete course

^a^ Arends et al., 2013; ^b^ Respondents could also indicate ‘*other conditions not listed*’.

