#### Medication use and change of medication

Use of medication is asked with an open-ended question: ‘*What medications do you currently use, as prescribed by your rheumatologist?*’ Furthermore, changes in medication are asked with the question: ‘*Has anything changed in your medication in the past two months?*’ Response options are: ‘*No*’ and ‘*Yes, I started a new drug. / I stopped a drug. / The dose of a drug is increased. / The dose of a drug has been reduced’ .*

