#### Direct medical costs

Medical costs are collected on a bimonthly basis. Patients are asked the number of telephone consultations they have with their GP, as well as their number of visits to the GP, medical specialist, other paramedical and alternative therapists, and hospital days.

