#### Indirect non-medical costs

Indirect non-medical costs are collected at the same frequency as the direct medical costs. Patients are asked about their absenteeism from work, domestic care, domestic help, and informal care.

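### Costs are collected at T0, but the Economic evaluation section gives them no role in the incremental cost or the ICER numerator

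*Protocol article*

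**What the plan says.** Table 3 in the Measurements section has the rows "Direct medical costs T0, T1, T2, T3, T4" and "Indirect non-medical costs T0, T1, T2, T3, T4". On frequency, the text says "Medical costs are collected on a bimonthly basis" and "Indirect non-medical costs are collected at the same frequency as the direct medical costs".

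The Economic evaluation section defines two periods for QALYs, "quality of life per time period (0–2 months and 0–8 months", and carries out the cost work per study period. For costs it plans arithmetic means with SDs per group, and then: "For every patient and study period, the mean incremental costs will be calculated, and, using double-sided bootstrapping, 95% confidence intervals (95%CI) will be estimated". For resource use: "The between-group differences in resource use will be analyzed per period using the Mann–Whitney U test". The ICER divides the extra costs by the extra QALYs. The section does not mention the T0 costs or any covariate.

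The article's only covariate rule is in the effectiveness analysis section. It concerns the primary and secondary outcomes, and it brings in a measure only if the arms differ significantly on it at baseline. Costs are not among those outcomes.

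**The concern.** Every participant is asked for a cost record that predates the programme, and the plan then compares costs as if that record did not exist. If a person's care use and sick leave persist from one window to the next, the T0 cost explains part of the variation in later cost. Leaving it out makes the interval for the incremental cost wider than it need be. It also lets a chance difference between the arms in earlier care use pass into the ICER numerator.

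Nothing else in the design controls this. Randomisation is stratified by site only, and the sample size is set on depressive symptoms. Cost-effectiveness is nonetheless a stated aim, and the Discussion predicts it.

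There is also a risk of misreading. Five cost forms are scheduled for a horizon that four of them fill, and the text does not say that the T0 form stays out of the total.

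**Working it through.** **1. The plan's own figure.** The article gives no figure for the cost comparison, so the only one to reproduce is the sample size (d = 0.40, power 0.80, two-sided alpha 0.05). n = 2(1.96 + 0.8416)²/0.40² = 98.1, so 99 per arm. The t-test version gives 99.08, so 100. The stated 100 per condition reproduces.

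**2. Where the T0 form falls.** The last follow-up is eight months after entry (Control condition), and T4 is six months after the programme ends (Measurements). T1 is therefore at about 8 − 6 = 2 months, and T2, T3 and T4 at about 4, 6 and 8 months. The T1–T4 forms fill 0–8 months, so T0 costs describe earlier time. The look-back of the T0 cost form is not stated. Two months is inferred from the bimonthly schedule and from the medication item, "Has anything changed in your medication in the past two months", which is also asked from T0 onward.

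**3. Assumptions.** The documents give no cost correlation. I assume five windows of equal length and variance, with two correlation patterns.

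**4. Gain for 0–8 months.** With adjustment the interval is multiplied by sqrt(1 − c²), where c = corr(T0 cost, sum of T1–T4 costs).

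Same correlation r between all windows, c = 4r/sqrt(4 + 12r):

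| r | c | interval factor |
|---|---|---|
| 0.3 | 0.435 | 0.90 |
| 0.4 | 0.539 | 0.84 |
| 0.5 | 0.632 | 0.77 |
| 0.6 | 0.717 | 0.70 |

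The interval is 10–30% narrower, and the residual variance 19–51% lower (c² = 0.19 to 0.51).

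Correlation decaying as a, a², a³, a⁴, c = (a + a² + a³ + a⁴)/sqrt(4 + 6a + 4a² + 2a³):

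| a | c | interval factor |
|---|---|---|
| 0.4 | 0.243 | 0.970 |
| 0.5 | 0.326 | 0.945 |
| 0.6 | 0.424 | 0.906 |
| 0.7 | 0.538 | 0.843 |

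The interval is 3–16% narrower.

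**5. Gain for 0–2 months.** Here c is simply the correlation of T0 with T1 cost, and the factor is sqrt(1 − c²): 0.95 at 0.3, 0.87 at 0.5, 0.71 at 0.7.

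**6. Chance imbalance.** At 100 per arm the standard error of the T0 difference is sqrt(2/100) = 0.141 SD of a two-month cost. At r = 0.5, an imbalance of one standard error carries 4 × 0.5 × 0.141 = 0.28 two-month SDs into the 8-month difference. The SD of the 8-month total is sqrt(4 + 12 × 0.5) = 3.16 two-month SDs. The shift is therefore 0.28/3.16 = 0.09 SD of the 8-month total, or 0.09/0.141 = about 0.63 of the standard error of that difference.

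**7. Skewed costs.** In a simulation with lognormal costs, 100 per arm, no true difference and 4,000 trials per setting, log-scale correlations of 0.3, 0.5 and 0.7 became raw correlations of about 0.22, 0.40 and 0.60. The ratio of adjusted to unadjusted standard error was 0.97, 0.92 and 0.77. Both estimators centred on zero. Skewness thus weakens the raw correlation and shrinks the gain without removing it.

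**The case against.** The strongest objection is that silence is being read as a decision. For resource use and QALYs the section names unadjusted tests. For incremental cost it names only a bootstrap interval, and an analysis plan that is not shown could add covariates. This stands in part: a reader might infer that the trial will never use the T0 costs, and the article shows only that the section gives them no role. It is still more than missing detail, because the section sets out the cost comparison and the ICER step by step, and the covariate rule elsewhere does not reach costs.

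The quoted sentence, with its per-patient wording, could also be taken to mean change from T0. The ICER definition points to a between-group difference, so I read it that way, but the wording is loose.

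A reader might also infer that the planned comparison is biased. It is not: under 1:1 randomisation the raw difference in means is unbiased, and its interval already allows for chance imbalance of the kind in step 6.

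Finally, the gain cannot be sized from the documents. They do not show that costs persist strongly within a person, and at a T0-to-follow-up correlation of 0.2 to 0.3 the standard error falls by only 2–5%. That objection stands in full.

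**Conclusion.** The point holds as one of efficiency. A baseline cost is collected, and the stated cost comparison gives it no role. The loss is precision and exposure to chance imbalance in earlier care use.

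The gain from adjustment for 0–8 months is roughly 3–30% in interval width. The lower part, 3–16%, applies if correlation decays over time, and skewness reduces it further. All of this rests on assumed correlations and on an inferred T0 window equal in length and variance to the later ones.

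Severity is modest. The trial is not sized on costs, and the section on strengths and limitations of the trial makes the economic evaluation conditional on an effect. The change is worth making because the data are already scheduled, and because fixing the adjustment beforehand prevents a choice after the results are seen.

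**What to change.** In the Economic evaluation section:

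- Define the incremental cost for each period as the arm coefficient from a regression of period cost on arm and T0 cost. Use the T1 form for 0–2 months and the T1–T4 forms for 0–8 months.
- Fit this model whatever a baseline significance test shows.
- Refit it in each bootstrap resample, jointly with the QALY difference, so that the same adjusted cost difference feeds the ICER and its interval.
- State that T0 costs are added to neither total, and state the look-back period of the T0 cost form.

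The cost is some wording, a few lines of code and a rule for participants without a T0 cost form. No new data are needed.
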